### Study monitoring

#### Data monitoring

The coordinating investigator will visit study centres every 3 months to discuss any issues and check on conduct of the study. Prior to recruitment, the field team (physicians) will receive information and instructions on the objectives of the study, methods and processes of the study. CRF data will be monitored by an independent external expert at regular intervals throughout the study to verify adherence to the protocol and data completeness, consistency and accuracy.

#### Data Safety Monitoring Board (DSMB)

In order to increase the safety of the intervention the trial will be monitored by an independent Data Safety Monitoring Board (DSMB). The DSMB will work in accordance with a dedicated charter and will follow processes recommended by the DAMOCLES Statement. The DSMB will be chaired by a neurosurgeon, and include a neurologist and an independent methodologist/statistician. The DSMB will meet at least annually or after inclusion of the next 150 patients (whichever comes first). With respect to study safety and efficacy, interim analyses of major endpoints (including serious adverse events believed to be due to treatment) are performed after 150 and 300 patients have completed their follow-up evaluation. In addition, the DSMB will review the study logistics/trial conduct in terms of: assessment of compliance with the study protocol (including adherence to inclusion and exclusion criteria) and monitor data quality (completeness), time to start of the procedure (DXM/surgery), cross-overs, occurrence and listing/registration of (serious) adverse events, by centre and by treatment arm.

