## Methods/Design

### Trial design

This is a prospective, multicentre, open-label, randomised controlled trial (RCT) with a blinded endpoint (PROBE design) assessment [16]. Eligible patients are randomised to DXM therapy (the intervention arm) or BHC (control arm; see Additional file 1 for SPIRIT check-list).

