#### Secondary outcome measures

Secondary outcomes include: functional and clinical outcome, expressed by mRS and MGS scores, respectively, at discharge, at 2 weeks, at 3, 6 and 12 months after start of study treatment. We will also determine a utility-weighted mRS (UW-mRS) at 3 months. The GOSE score will be assessed at 3 months, quality of life (expressed by SF-36 and QOLIBRI) at 3 and 12 months, cost-effectiveness at 3 and 12 months and haematoma thickness at 2 weeks. During the first 12 months, we will evaluate haematoma recurrence (defined as recurrence of symptoms and neurological signs after initial improvement with persistence, recurrence or increase of CSDH on follow-up CT), failure of therapy after randomisation and requiring intervention, complications and drug-related adverse events, duration of hospital stay and healthcare and productivity costs in both patient groups. Finally, we will evaluate mortality during the first 3 and 12 months.

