#### Adverse events (AEs) and serious adverse events (SAEs)

Adverse events are defined as any undesirable event occurring to a patient during the study, whether or not considered related to DXM therapy or surgery. All adverse events reported spontaneously by the patient or observed by the investigator or staff will be recorded. A SAE is any untoward medical occurrence or effect that results in death; is life-threatening (at the time of the event); requires hospitalisation or prolongation of existing inpatients’ hospitalisation; results in persistent or significant disability or incapacity or any other important medical event that did not result in any of the outcomes listed above due to medical or surgical intervention, but could have been based upon appropriate judgement by the investigator. SAEs are reported by the investigators in participating centres to the coordinating investigator. SAEs will be reported through the web portal *ToetsingOnline* to the accredited Medical Ethics Committee that approved the protocol.

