#### Interim analysis

Interim analyses of major endpoints (including serious adverse events believed to be due to treatment) are performed after 150 and 300 patients have completed their follow-up evaluation.

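### The interim comparison of serious adverse events is limited to those attributed to treatment in an open-label trial, so it can under-count harm in the DXM arm

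*Protocol article*

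**What the plan says.** The section on the Data Safety Monitoring Board sets out, for safety and efficacy, this rule: "interim analyses of major endpoints (including serious adverse events believed to be due to treatment) are performed after 150 and 300 patients". The counts refer to patients whose follow-up is complete. The section Interim analysis gives the same rule: "Interim analyses of major endpoints (including serious adverse events believed to be due to treatment) are performed after 150 and 300 patients have completed". The other major endpoints are not named in either place.

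The section on adverse events takes the wider view. An adverse event there is "any undesirable event occurring to a patient during the study, whether or not considered related to DXM therapy or surgery", and all such events, reported or observed, are recorded.

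The section Trial design describes a "prospective, multicentre, open-label, randomised controlled trial (RCT) with a blinded endpoint (PROBE design) assessment". The blinding detailed later concerns the research nurse who scores the 3-month mRS by phone. SAEs are reported by the investigators at the sites to the coordinating investigator, and no blinded or independent assessment of cause is described.

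The secondary outcomes over 12 months, evaluated in both groups, include "failure of therapy after randomisation and requiring intervention, complications and drug-related adverse events".

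The DSMB section adds a review of logistics and trial conduct. This covers "time to start of the procedure (DXM/surgery), cross-overs" and "occurrence and listing/registration of (serious) adverse events, by centre and by treatment arm".

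**The concern.** The two arms can harm patients in different ways, and an attribution filter need not treat those ways alike. Under BHC, the specific harms are complications of an operation, which are easily ascribed to it. Under primary DXM, one specific risk is that the haematoma is not evacuated and the patient deteriorates. A physician who knows the allocation may ascribe that to the chronic subdural haematoma, or to lack of effect, rather than to treatment. Such an event would drop out of the interim SAE comparison on the DXM side, while its surgical counterpart would stay in on the BHC side.

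At stake is the ability of the interim SAE comparison to show an excess of serious harm in the DXM arm. The comparison could look balanced while all-cause SAEs are not, and how balanced it looks would depend on unblinded opinion.

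The secondary outcome raises a smaller, related issue. If the drug meant is DXM, a BHC patient who never receives it cannot have a drug-related event, although infection, hyperglycaemia, gastro-intestinal bleeding or psychiatric symptoms can occur in either arm.

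**Working it through.** **Reading the sections together.** The plan states no figure on this point, so there is none to reproduce. The argument rests on four steps.

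1. *Collected:* all adverse events, related or not (section on adverse events).
2. *Compared at the interim looks:* only the SAEs attributed to treatment (DSMB and Interim analysis sections). This is a stated rule, not a gap in the article.
3. *Who judges cause:* no blinded or independent assessor is described, and treatment is open-label.
4. *Does treatment-related harm include harm from leaving the haematoma in place?* The text does not say. The section Investigational treatment points away from it: its reasons for discontinuing DXM list lack of improvement and clinical deterioration separately from DXM-related side effects or complications. An investigator who follows that division would not call deterioration DXM-related.

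**Illustration of size.** All rates below are assumed, because the documents give no SAE rates. With 1:1 allocation, the looks at 150 and 300 patients have 75 and 150 per arm.

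- Both arms: 10% SAEs unrelated to treatment, never attributed to it.
- BHC: a further 10% related to surgery, always attributed. All-cause 10% + 10% = 20%.
- DXM: a further 10% related to the drug, always attributed, and 10% from delayed or withheld surgery, of which a share f is attributed. All-cause 10% + 10% + 10% = 30%.

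Filtered rates: DXM = 10% + f × 10%; BHC = 10%.

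Power of a two-sided 5% test with n per arm, where d is the difference and p̄ the mean of the two rates:

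Φ{ [d − 1.96·√(2p̄(1−p̄)/n)] / √[(p₁(1−p₁)+p₂(1−p₂))/n] }

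For all-cause SAEs at n = 75: (0.10 − 1.96 × 0.0707) / 0.0702 = −0.549, and Φ(−0.549) = 0.29.

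| Comparison | DXM vs BHC | Expected SAEs at 75 per arm | Power, 150 patients | Power, 300 patients |
|---|---|---|---|---|
| All-cause | 30% vs 20% | 22.5 vs 15 | 29% | 52% |
| Filtered, f = 100% | 20% vs 10% | 15 vs 7.5 | 40% | 68% |
| Filtered, f = 75% | 17.5% vs 10% | 13.1 vs 7.5 | 26% | 47% |
| Filtered, f = 50% | 15% vs 10% | 11.25 vs 7.5 | 15% | 26% |
| Filtered, f = 25% | 12.5% vs 10% | 9.4 vs 7.5 | 7% | 10% |
| Filtered, f = 0% | 10% vs 10% | 7.5 vs 7.5 | no difference to detect | no difference to detect |

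The filter does not always hurt. If all delay-related harm is attributed to treatment, it removes background events and power rises (40% against 29% at the first look). At 75% attribution it is already slightly worse than the all-cause comparison, and at 0% the excess is gone. The same true excess can thus appear in full or vanish, according to a judgement that is not blinded.

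**The case against.** A reader might infer that harm from delaying or withholding surgery is nowhere counted against DXM. The protocol does not support that. Mortality at 3 and 12 months, failure of therapy requiring intervention, recurrence, MGS and mRS (with death as category 6) carry no causal filter. All arm comparisons follow intention to treat, so events after cross-over to surgery stay with the DXM arm. The interim rule also speaks of major endpoints that include the attributed SAEs, so these are one component of the review. The DSMB further sees adverse events and cross-overs by arm without a relatedness condition. All of this stands. It is only a partial offset: the article does not say which of those outcomes are interim endpoints, the by-arm review is placed under logistics and trial conduct, and no all-cause SAE comparison between arms is named anywhere.

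A reader might also infer that safety in the BHC arm has no counterpart to drug-related events. That too goes beyond the text. The same outcome item includes complications, which has no causal qualifier, covers both groups and has a named logistic regression. What remains is that complications are not defined in the article and that drug-related events on their own are one-sided.

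A third tempting step is to size the loss from the 25% of patients who needed surgery after initial DXM in a retrospective study cited in the Discussion (0.25 × 75, about 19 patients at the first look). That is not an SAE rate, and those patients would count as therapy failures and be visible as cross-overs.

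Finally, no section says that investigators will ascribe deterioration to the disease, and treatment-related could be read to cover the allocated strategy. The DSMB charter and the SAP are not shown and may add all-cause tables. If they do, the rule in these two sections would still need to be aligned with them.

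**Conclusion.** The point holds in a limited form. The protocol fixes the SAE part of its interim analyses on attributed events, in an open-label trial without a described blinded review of cause, although it records all events. The named comparison can therefore under-count serious harm in the DXM arm. It does not follow that such harm goes unseen, since other outcomes and the DSMB's by-arm review catch part of it.

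The size cannot be derived from the documents. Under the assumed all-cause rates of 30% vs 20%, the filtered comparison lies between 20% vs 10% and 10% vs 10%, and power at the first look lies anywhere from 40% down to no detectable difference, against 29% for all-cause SAEs. The range depends wholly on the share of delay-related events attributed to treatment. The illustration also assumes that drug- and surgery-related SAEs are always attributed correctly.

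For the secondary outcome, the conclusion is only that drug-related events cannot by themselves give a between-arm excess risk. The point is worth correcting because it concerns patient protection and the correction is nearly free.

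**What to change.** - **DSMB and Interim analysis sections:** base the interim SAE comparison on all deaths and all SAEs by randomised arm, irrespective of attributed cause. Show attribution as a supplementary column, preferably assessed blind to allocation.
- **Secondary outcome measures:** compare all-cause SAEs and one common list of adverse events in both arms. The list can include infection and the events the protocol already names for DXM (hyperglycaemia, gastro-intestinal bleeding, psychiatric symptoms). Keep drug-related as a supplementary classification.
- **Charter and SAP:** check that both use the same definition.

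The cost is a wording change and slightly longer tables. The all-cause comparison needs no new data, because all adverse events are already recorded. Only a blinded attribution, if adopted, would add work.

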#### Adverse events (AEs) and serious adverse events (SAEs)

Adverse events are defined as any undesirable event occurring to a patient during the study, whether or not considered related to DXM therapy or surgery. All adverse events reported spontaneously by the patient or observed by the investigator or staff will be recorded. A SAE is any untoward medical occurrence or effect that results in death; is life-threatening (at the time of the event); requires hospitalisation or prolongation of existing inpatients’ hospitalisation; results in persistent or significant disability or incapacity or any other important medical event that did not result in any of the outcomes listed above due to medical or surgical intervention, but could have been based upon appropriate judgement by the investigator. SAEs are reported by the investigators in participating centres to the coordinating investigator. SAEs will be reported through the web portal *ToetsingOnline* to the accredited Medical Ethics Committee that approved the protocol.

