**Fig. 2 Fig2:**
[figure not shown]
Flow diagram of main study procedures

In summary, study patients will be evaluated at presentation (baseline), during their hospital stay, at discharge and during the follow-up period at 2 weeks, 3 months, 6 months and 12 months.

At 2 weeks (after initiation of the study treatment) patients will be evaluated by neurological examination combined with a follow-up CT scan at the outpatient clinic or ward and at 3 months at the outpatient clinic. A mRS-certified research nurse, blinded for treatment allocation, will evaluate the primary outcome (mRS score) at 3 months by phone. At 3 and 12 months, patients will receive questionnaires on quality of life. Additionally, an evaluation of mRS score will take place by phone at 3, 6 and 12 months. Healthcare and productivity costs will be evaluated at 3 and 12 months. We expect to complete patient inclusion in 3 years. The estimated duration of the study (including follow-up) will be 4 years.

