### Interventions

#### Investigational treatment

Patients in the intervention arm will receive DXM in a daily dosage of 16 mg (8 mg every 12 h) on days 1 to 4. Thereafter, DXM will be tapered by half every 3 days (see Table 4 for the DXM dosing scheme) until a dosage of 0.5 mg a day on day 19 and stopped on day 20. DXM is administered orally in tablets or intravenously when oral administration is not possible. If the patient improves on DXM therapy (defined by ≥ 1 point decrease in MGS score) during the first 2 weeks, the treatment will be continued until day 19. During DXM treatment a proton pump inhibitor (pantoprazole, 40 mg daily) is administered as prophylaxis.

**Table 4 Tab4:** Dexamethasone (DXM) dosing scheme

Day	DXM dosage
1–4	8 mg every 12 h
5–7	4 mg every 12 h
8–10	2 mg every 12 h
11–13	1 mg every 12 h
14–16	0.5 mg every 12 h
17–19	0.5 mg per day
20	Stop

DXM therapy can be discontinued for the following reasons: (1) no improvement of the clinical condition, defined as an unchanged MGS score 2 weeks after initiation of DXM therapy with unchanged or increased haematoma on the follow-up CT at 2 weeks, (2) clinical deterioration, defined by as ≥ 1 point increase in MGS score, at any time after initiation of DXM treatment, (3) the occurrence of severe, relevant DXM-related side effects or complications (i.e. uncontrollable hyperglycaemia, gastro-intestinal bleeding or psychiatric symptoms), (4) pre-study complement discontinuation of DXM therapy is primarily left to the discretion of the treating physician and is recommended in case of: persistence of moderate to severe neurological symptoms (MGS grade 2–3) in combination with the presence of relevant severe, current comorbidities (i.e. an infection, metabolic deterioration) which could interfere with the expected recovery, and a surgical intervention could be beneficial and the safest option for patient recovery.

In any case of pre-study discontinuation of DXM therapy, the reason for this is documented. Whenever DXM is discontinued, a cross-over to the reference treatment (BHC) can occur depending on the remaining symptoms, which is the local standard of care in the participating hospitals.

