#### Concomitant care

All included patients will otherwise receive routine standard of care. Patients with mild neurological deficits (MGS grade 1) on admission can be discharged home in anticipation of the planned BHC or awaiting the effect of DXM therapy. However, in MGS grade 1 patients with known diabetes mellitus (DM) with HbA1C < 64 mmol/mol randomised for DXM therapy, monitoring for blood glucose levels is necessary during the first 3 days after treatment initiation. Glucose monitoring can take place clinically during admission or if possible at the nursing home. Patients with MGS grade 2–3 (in either arm) remain in hospital until the treating physician judges the clinical situation safe for discharge.

During admission neurological investigations and vital parameters are recorded daily. Low-molecular-weight heparin (LMWH) will be applied in both patient groups as thrombosis prophylaxis if the patient is not optimally mobile. Patients will receive physiotherapy, speech therapy or rehabilitation consultation if deemed necessary.

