Uncertainty around this ratio will be presented using confidence eclipses on the cost-effectiveness plane and acceptability curves. We will perform a sensitivity analysis to assess the robustness of the results to changes in costs and effectiveness parameters. Due to the short time horizon, no discounting for costs and effects will be used (see Additional file 2 for statistical analysis plan).

For secondary endpoint parameters, Kaplan-Meier and Cox regression analysis will be used for mortality comparisons between the treatment arms, binary logistic regression for complications and failure of therapy, and a linear regression to evaluate quality of life. A *p* value of less than 0.05 will be used to indicate statistical significance. For all analyses, R statistical software will be used.

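### Adverse events are captured passively in an open-label trial whose care settings differ by arm for MGS 1 patients, so detection of milder events may differ between arms

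*Protocol article*

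**What the plan says.** **Capture.** The section on adverse events (AEs) and serious adverse events states: "All adverse events reported spontaneously by the patient or observed by the investigator or staff will be recorded". Both routes it names are passive. The article describes no checklist or fixed question.

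**Use of the data.** Under Secondary outcome measures, the 12-month outcomes include "complications and drug-related adverse events, duration of hospital stay and healthcare and productivity costs in both patient groups". Data analysis assigns "binary logistic regression for complications and failure of therapy". The Data Safety Monitoring Board section has the board review listings of adverse events by treatment arm.

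**Blinding.** Trial design describes an open-label trial with blinded endpoint assessment. The blinded assessment actually described, under Participant timeline, is the 3-month modified Rankin Scale (mRS) telephone call.

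**Setting.** Under Concomitant care, patients with Markwalder Grading Scale (MGS) grade 1 "can be discharged home in anticipation of the planned BHC or awaiting the effect of DXM therapy". For the higher grades: "Patients with MGS grade 2–3 (in either arm) remain in hospital until the treating physician judges the clinical situation safe for discharge". For inpatients: "During admission neurological investigations and vital parameters are recorded daily". Reference treatment specifies a subdural drain for 2 days after BHC.

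**Timing.** Investigational treatment tapers DXM "until a dosage of 0.5 mg a day on day 19 and stopped on day 20". Participant timeline schedules evaluations at baseline, in hospital, "at discharge and during the follow-up period at 2 weeks, 3 months, 6 months and 12 months". These contacts are the same in both arms.

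**The concern.** When recording depends on what a patient volunteers or staff happen to see, the recorded rate depends on how closely the patient is watched. Here that can differ by arm during the exposure itself. A BHC patient is under staff observation during the operation and drainage. An MGS 1 patient on DXM may spend the exposure at home, where milder events such as raised glucose, mood change or a minor infection may be recorded only if the patient mentions them. The Background says the disease generally affects the elderly, so unprompted recall weeks later is a weak instrument.

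At stake is a planned between-arm comparison and part of what the monitoring board sees. Logistic regression cannot repair unequal ascertainment. If DXM events are under-counted, the error favours the experimental arm, and in a non-inferiority trial the safety comparison is read alongside the functional result.

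**Working it through.** The plan gives no figure for this point, so there is none to reproduce. The check has two parts.

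**1. Exposure set against observation**

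| | BHC | DXM |
|---|---|---|
| MGS 1 | May wait at home before surgery; in care for the operation and the 2-day drain (inpatient stay inferred) | May be at home during the course |
| MGS 2–3 | In hospital until judged safe for discharge | Same |
| Contacts after discharge | 2 weeks, 3, 6 and 12 months | Same |
| Extra monitoring | None described | Glucose for the first 3 days in MGS 1 patients with known diabetes |

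Dates, taking the 2-week visit as day 14 and 3 months as day 91:
- visit to last DXM dose: 19 − 14 = 5 days
- visit to next scheduled contact: 91 − 14 = 77 days
- last dose to next scheduled contact: 91 − 19 = 72 days

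The 77-day interval is the same in both arms. What is specific to DXM is that treatment may be taken at home and that its last days and withdrawal fall inside that interval. The difference in setting therefore lies mainly in MGS 1 patients around treatment.

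**2. How large could the effect be?**

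None of the rates below is in the documents; all are assumptions. Let the true event rate be p in both arms, with complete detection under BHC. A share h of DXM patients is at home, with relative detection s there. The observed DXM rate is

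q = p(1 − h + hs) = p[1 − h(1 − s)],

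and the observed odds ratio, DXM versus BHC, is [q/(1 − q)] / [p/(1 − p)].

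The grid is p = 10, 20, 30, 40%; h = 30, 60%; s = 0.6, 0.8, 0.9, which makes 24 scenarios. The arm-level loss h(1 − s) takes four values: 3% (0.3 × 0.1), 6% (0.3 × 0.2 or 0.6 × 0.1), 12% (0.3 × 0.4 or 0.6 × 0.2) and 24% (0.6 × 0.4). Cells show the observed odds ratio. In brackets is the chance of a nominally significant lower DXM rate, from a two-sided 5% normal-approximation test of two proportions with 210 per arm. This counts only the tail in DXM's favour, so its value with no detection loss is 2.5%.

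| p | loss 3% | loss 6% | loss 12% | loss 24% |
|---|---|---|---|---|
| 10% | 0.97 (3.2%) | 0.93 (4.0%) | 0.87 (6.2%) | 0.74 (13.7%) |
| 20% | 0.96 (3.6%) | 0.93 (5.0%) | 0.85 (9.2%) | 0.72 (25.2%) |
| 30% | 0.96 (3.9%) | 0.92 (6.0%) | 0.84 (12.7%) | 0.69 (38.7%) |
| 40% | 0.95 (4.4%) | 0.90 (7.3%) | 0.81 (17.2%) | 0.66 (54.0%) |

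Worked example, the largest: p = 0.40, h = 0.6, s = 0.6 gives q = 0.40 × (1 − 0.24) = 0.304, and (0.304/0.696)/(0.40/0.60) = 0.66.

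The 6% and 12% columns each stand for two scenarios per row. The chance is below 8% in 4 (loss 3%) + 8 (loss 6%) + 2 (loss 12% at p = 10%) = 14 of the 24. The effect runs from negligible to material, and the assumed loss decides which.

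**The case against.** **The sentence does not exclude asking.** It says what must be recorded, and the word *only* is not in it. A structured form may sit in the CRF, the full protocol or the schedule figure, none of which is shown. This stands, so no absence from the trial as a whole can be claimed. What remains is that the method the article does state is passive, and a better one costs little.

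**Whole arms do not differ in setting.** A reader might infer that BHC patients are always in hospital and DXM patients at home. The text does not support that: MGS 1 patients may go home in either arm, and MGS 2–3 patients stay in either arm. The contrast survives for MGS 1 patients around treatment.

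**The long gap is shared.** A reader might treat the interval from 2 weeks to 3 months as a gap in the DXM arm alone, or the 2-week visit as the last contact. Neither is so: BHC patients have the same interval, and both arms have three later contacts.

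**The direction is not shown.** Glucose monitoring in known diabetics, a named outcome of drug-related events, and side effects listed as reasons to stop DXM all draw attention to DXM events, and open-label awareness could raise their reporting. This stands in part. The glucose monitoring lasts 3 days, covers only MGS 1 patients with known diabetes, and does not reach mood symptoms or infection.

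**The stakes are limited.** The primary outcomes are the mRS and cost-effectiveness; complications are one secondary outcome among many. Serious events such as death or hospitalisation depend less on setting. Both points stand.

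**Conclusion.** The point holds as a risk. Passive capture in an open-label trial, with a different care setting for MGS 1 patients during exposure, may make detection of milder, non-serious events differ by arm. Under-counting of DXM events is the plausible direction but is not established.

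The documents give no size. With equal true rates of 10–40%, 30–60% of DXM patients at home and relative detection of 0.6–0.9 there, the observed odds ratio runs from about 0.97 to 0.66. All these inputs are assumed.

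A reader might construct a starker figure. A true rate of 30%, with detection of 90% under BHC and 60% under DXM, gives 27% versus 18% and an odds ratio of (0.18/0.82)/(0.27/0.73) = 0.59. The arithmetic is right, but it applies the loss to every DXM patient. If half were at home and the rest were detected at 90%, home detection would have to be 30%, since 0.5 × 0.90 + 0.5 × 0.30 = 0.60. Nothing in the documents supports that, nor a statement that the comparison is biased towards DXM. This is a cheap improvement to a secondary safety comparison; it does not touch the primary analysis.

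**What to change.** In the section on adverse events, add one fixed list of questions asked in the same words in both arms at each existing contact (2 weeks, 3, 6 and 12 months).

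- **Content:** the DXM-related events named under Investigational treatment, surgical complications, infection, readmission and new treatment, each with an onset date. Surgical complications must be on the list, or it could tilt detection the other way.
- **At 3 months:** ask explicitly about the period since the 2-week visit. Site staff should ask at the outpatient visit, separately from the blinded mRS call.
- **At 6 and 12 months:** ask after the mRS has been scored.
- **Spontaneous reports:** keep them as an addition.
- **If the CRF already holds such a list:** align the sentence with it.

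The cost is one CRF page, a few minutes per contact and more minor events to record, with no new visits. Recall between 2 weeks and 3 months remains imperfect because no contact is added, but patients in both arms are then prompted in the same way. The change helps whichever way detection would otherwise differ.
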